### 3.TREATMENT OF SUBJECTS

#### INTERVENTION

Genotyping: For eligible patients genetic variants that affect the metabolising capacity of CYP2D6 and CYP2C19 will be determined. These variants explain in 90-95% of the cases with changes in CYP2D6 and CYP2C19 enzyme activity (see Appendix A). Dedicated genotyping methods will be used for the detection of the relevant genetic variants. Both labs that will perform genotyping take part in interlaboratory quality control programs.

Based on the drug choice and based on the latest allele definition tables (as present in the KNMP kennisbank achtergrondteksten) each patient will be classified into a metabolic phenotype category (PM,IM,EM or UM; see Appendix B).

Strategy 1: Genotype-guided dosing with Therapeutic Drug Monitoring (100 patients). In these patients, initial dosing of the TCAs will take place according to the pharmacogenetic dosing guidelines by the KNMP (<https://kennisbank.knmp.nl>; see Appendix C). These guidelines recommend specific dose adaptations for each of the metabolizer genotypes and for each type of TCA. The initial dose advice is communicated to the treating physician. In agreement with common practice, each time a steady-state can be expected (7 days after the last dose change) plasma concentrations of TCA and active metabolites will be measured. If the predefined therapeutic level has not been reached yet, further dose adaptations will be communicated, based on a predetermined dosing algorithm that considers linear pharmacokinetics of TCAs. This procedure will be repeated until a therapeutic level at steady state has been reached (endpoint of primary outcome).

Strategy 2: Standard dosing with Therapeutic Drug Monitoring (100 patients). In these patients, initial dosing of TCA will be performed according to standard Dutch dosing guidelines (Farmacotherapeutisch Kompas). According to these guidelines the recommended starting dose per drug is given which is gradually increased during the first week until the standard dose is reached. When steady-state has been achieved for the standard dose (7 days later), plasma concentrations will be measured and dosing will be further adjusted using the same dosing algorithm based on linear kinetics (Birkenhäger and Moleman 2007) until a therapeutic level at steady state has been reached (as described under strategy 1).

In additional analyses we will compare the results of the deviant metabolizer groups with those of patients with this normal metabolism phenotype. Before inclusion, all patients will have signed the informed consent form.

**3.1 Investigational product/treatment**

Not applicable.

**3.2 Use of co-intervention (if applicable)**

Not applicable

**3.3 Escape medication (if applicable)**

Not applicable

**4. INVESTIGATIONAL PRODUCT**

This section is not applicable.

- 4.1 Name and description of investigational product(s)**
- 4.2 Summary of findings from non-clinical studies**
- 4.3 Summary of findings from clinical studies**
- 4.4 Summary of known and potential risks and benefits**
- 4.5 Description and justification of route of administration and dosage**
- 4.6 Dosages, dosage modifications and method of administration**
- 4.7 Preparation and labelling of Investigational Medicinal Product**
- 4.8 Drug accountability**

## **5. NON-INVESTIGATIONAL PRODUCT**

This section is not applicable. The drugs used for treatment in this study (imipramine, clomipramine and nortriptyline) are regularly prescribed and registered drugs. For product details we refer to the Summary of Product Characteristics (SPC) at the CBG website <https://db.cbg-meb.nl>.

- 5.1 Name and description of non-investigational product(s)**
- 5.2 Summary of findings from non-clinical studies**
- 5.3 Summary of findings from clinical studies**
- 5.4 Summary of known and potential risks and benefits**
- 5.5 Description and justification of route of administration and dosage**
- 5.6 Dosages, dosage modifications and method of administration**
- 5.7 Preparation and labelling of Non Investigational Medicinal Product**
- 5.8 Drug accountability**

## 6. METHODS

### 6.1 Study parameters/endpoints OUTCOME PARAMETERS:

#### 6.1.1 Main study parameter/endpoint

1. Primary outcome measure: Time to TCA plasma concentration in the therapeutic range (primary outcome measure). Serum/plasma for plasma concentration measurements will be taken in the morning, at 10-16 hours after the last evening dose when prescribed once daily. For patients with a two or three daily regime, plasma concentration measurement will be taken in the morning before morning dose. Concentrations will be measured using validated liquid chromatography (LC) assays, to be performed by the clinical pharmaceutical laboratories associated with the centres where patients are included. Assays for TCAs performed well in interlaboratory quality control (proficiency testing) programs and will be cross validated. TCA plasma concentration assessments are performed at steady state (after 7 days of a stable dose) and as described before, dose adaptations are based on these measurements using a predetermined dosing algorithm. When a patient attains a plasma level within the therapeutic range at steady state, the primary endpoint has been reached (for nortriptyline 0.05–0.15 mg/l; for clomipramine: 0.2–0.30 mg/l (clomipramine plus desmethylclomipramine) and for imipramine 0.15-0.3 mg/l (imipramine plus desipramine).

#### 6.1.2 Secondary study parameters/endpoints (if applicable)

a. **Reduction of depressive symptoms after 7 weeks of treatment** (defined as the baseline HAM-D score (Hamilton 1960) minus the HAM-D score at the 7 weeks assessment.) rated by a blinded investigator and the reduction on the QIDS-SR (Rush et al. 1986) rated by the patients themselves.

b. **Highest level of side effects** based on the Antidepressant Side Effect Checklist (ASEC, Uher et al. 2009) and the FIBSER (Frequency, Intensity, and Burden of Side Effects Rating FIBSER (Wisniewski et al. 2006)) rated by the patient.

c. **Economic Evaluation:**

The impact of the intervention on the quality of life of patients will be assessed both by the EuroQol 5 dimensions with 5 levels (EQ5D5L; Lamers et al. 2005) and the The Short Form (36) Health Survey (SF36; RUG 1993) at weeks 0, 2, 4, 6, 13 and 26 following randomization.

Cost analysis: The cost analysis consists of two main parts. First, at patient level, volumes of care related to MDD and TCA therapy will be measured by means of the iMTA Medical Consumption Questionnaire. This questionnaire measures all relevant health care related costs like outpatient visits at any medical specialist and hospitalizations. In addition the medication use will be derived from the electronic patient records. Loss of productivity due to illness or recovery, will be estimated based on patient reported absences from paid (or unpaid) labour measured with the Productivity Cost Questionnaire.

The second part of the cost analysis consists of determining the cost prices for each volume of consumption. The standard cost prices from the 'Dutch Guidelines for Cost Analyses' and [www.medicijnkosten.nl](http://www.medicijnkosten.nl) will be used. For units of care where no standard prices are available real costs prices will be determined on the basis of full cost pricing. Productivity losses will be valued by means of the friction cost method. In the end volumes of care will be multiplied with the cost prices for each volume of care to calculate costs.

For more detailed information regarding the economic evaluation see the study description below (7.3).

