The overall aim of the present study is to provide the evidence base for pharmacogenetics based dosing of TCAs in patients with severe MDD. To this end we will make a direct comparison between (a) genotype-based dosing (according to the Dutch guidelines of the KNMP) supplemented with Therapeutic Drug Monitoring (TDM) and (b) dosing as usual supplemented with TDM. We hypothesize that personalized genotype-guided dosing of TCAs results in faster achievement of therapeutic serum/plasma levels and consequently earlier reductions of depressive symptoms and reductions of adverse effects and reductions in healthcare costs and costs related to work impairment compared to dosing as usual.

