### Secondary Objectives:

- To assess whether genotype guided dosing results in lower rates of adverse effects compared to dosing as usual. .
- To assess whether genotype guided dosing results in earlier reductions of depressive symptoms compared to dosing as usual. .
- To assess the value of an early TCA serum/plasma level (12 hours after the first dose) as a potential predictor of time to therapeutic plasma concentration, treatment response and side effects.

- To explore the predictive value of other clinical (psychomotor retardation) and biological factors (measures of metabolomics) and the changes within these factors during treatment to therapeutic plasma concentration, treatment response and side effects.
- To compare the healthcare costs and work related costs of genotype based dosing to dosing as usual.

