**Study procedure:**

Visit 1 (Inclusion and genotyping): All eligible patients will be asked to provide written informed consent. Inclusion and exclusion criteria are checked and baseline and demographic variables will be collected (complete somatic and psychiatric history, physical examination, inventory of medication and use of drugs, and laboratory studies equivalent to the procedures in standard clinical care).

Genotyping: For eligible patients relevant genetic variants in *CYP2D6* and *CYP2C19* will be determined. These variants explain in 90-95% of the cases with changes in *CYP2D6* and *CYP2C19* enzyme activity.

Based on the drug choice and based on the latest allele definition tables (KNMP kennisbank achtergrondteksten) each patient will be classified into a metabolic phenotype category (PM,IM,EM or UM).

The time period between visits 1 and 2 will be used for washout of psychiatric drugs to which insufficient response occurred and/or that interfere with study medication (also in accordance to standard clinical procedures). Genotype information and the consequent drug dosing advice will be available within five working days after visit 1.

Visit 2: Baseline (start TCA therapy). Completion of baseline assessments of secondary clinical outcome measures. During this visit TCA treatment will be started according to the instructions per treatment strategy group (genotype guided dosing vs. dosing as usual). TCAs will be initially prescribed once daily in the evening, although the dosing regimen can later on be altered according to the patient preference. The TCAs will be prescribed and delivered by either the in-hospital or outpatient pharmacy, dependent on the situation of the patient.

Visits 3 to 9 treatment phase: During seven weeks the patients receive TCA treatment based on the dosing instructions as described above (Strategies 1 and 2). Patient assessments will take place weekly for (a) TCA concentration measurements if indicated (see description) (b) the secondary clinical outcome measures as described under visit 1 (side effects and depressive symptoms). Adherence to drug treatment will be checked weekly either by review of a drug diary kept by the patient or by interviewing the patient during visits.

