### 8.2 Secondary study parameter(s)

The secondary continuous outcomes will be analysed by either student's t-test or Mann Withney U test dependent on the normal distribution of data or not. For the HAM-D scores we will compute the reduction as the baseline scores minus the scores at 7 weeks of treatment. FIBSER scores for side effects will be reported as means and standard deviations; qualitative details of the side effects will also be provided. For all statistical test we will use a significance level of 5% (two-sided). For missing values we will use the most recent HAM-D score that is available before the end of the medication study (7 weeks). For the FIBSER we will use the highest level of side effects measured during the medication study.

In additional analyses we will compare the primary and secondary outcome measures of the deviant metabolizer groups with those of patients with the normal metabolism phenotype.

Multiple regression analysis will be used to study the predictive effects of the early TCA serum/plasma level and other clinical (psychomotor retardation) and biological factors on the primary and secondary outcome measures (see research questions).

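### The depression objective asks whether symptoms fall earlier, but the only depression outcome is a single week-7 change, which measures how much rather than how soon

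*Protocol*

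**What the plan says.** The question is one of timing. The Protocol's Objectives section (repeated in the Summary) sets out "To assess whether genotype guided dosing results in earlier reductions of depressive symptoms compared to dosing as usual", and Section 1 expects faster therapeutic levels and "consequently earlier reductions of depressive symptoms".

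The outcome is a single time point. Section 6.1.2 names "Reduction of depressive symptoms after 7 weeks of treatment". For the clinician-rated scale this is then "defined as the baseline HAM-D score (Hamilton 1960) minus the HAM-D score at the 7 weeks assessment"; the patient-rated QIDS-SR reduction is listed beside it. Section 8.2 fixes the same variable for analysis: "For the HAM-D scores we will compute the reduction as the baseline scores minus the scores at 7 weeks of treatment". On the test it says: "The secondary continuous outcomes will be analysed by either student's t-test or Mann Withney U test". If the week-7 HAM-D is missing, the last score before it is used instead.

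The weekly data exist. The schedule in Section 6.3 has HAM-D and QIDS at baseline and at every visit from week 1 to week 7, and the procedure text says "Patient assessments will take place weekly for" these measures. No time-to-response, slope, area-under-curve or weekly contrast is stated for them. The repeated-measures design in Section 8.3 is for the economic analysis.

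**The concern.** A change score at one late visit answers how far patients have improved by then. Two arms that reach the same week-7 level at different speeds give no effect on it. If the arms do differ at week 7, the result shows a larger reduction and leaves open whether it came earlier. Neither a positive nor a null result therefore settles the timing question.

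A head start is also the mechanism the design relies on. Section 2.4 assumes median attainment of therapeutic levels at 2 weeks versus 4, and Section 3 adjusts both arms with the same algorithm until the level is reached, so some catch-up by controls within 7 weeks is plausible. At stake is the wording of a secondary conclusion: the trial could report earlier relief without evidence on timing, or overlook it although the weekly scores were recorded.

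**Working it through.** **The protocol's own figure.** Section 2.4 gives HAM-D reductions of 17.5 versus 13 (difference 4.5), SD 9, two-sided 5%, 80% power.

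n per arm = 2 × (1.96 + 0.842)² × 9² / 4.5² = 62.8, so 63, as stated. Power for a 4.5-point gap is 80.1% at 63 and 94.2% at 100 per arm. The sizing is correct for a gap of that size in the change score.

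**What a pure head start leaves at week 7.** The documents give no HAM-D trajectory, so these curves are assumptions: in each arm the mean reduction rises linearly from week s over D weeks to a common 15-point plateau, and the control curve starts 2 weeks later.

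- Reduction at week w = 15 × (w − s)/D, held between 0 and 15.
- Gap at week w = intervention minus control. Mean gap = average over weeks 1 to 7.
- Week-7 power: z = gap / (9 × √(2/100)) = gap / 1.273; power = Φ(z − 1.96) + Φ(−z − 1.96).
- Power of the 7-visit mean: the same formula with SD = 9 × √((1 + 6r)/7). The within-patient correlation r is assumed to be 0.5 to 0.7, giving SD 6.80 to 7.76.

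Example (starts at weeks 1 versus 3, D = 4): weekly gaps are 0, 3.75, 7.5, 7.5, 7.5, 3.75, 0. They sum to 30, so the mean is 30/7 = 4.29 and the week-7 gap is 0.

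| Start, intervention vs control (week) | Rise D (weeks) | Week-7 gap | Power, week 7 | Mean gap, weeks 1–7 | Power, mean |
|---|---|---|---|---|---|
| 1 vs 3 | 4 | 0 | 5% | 4.29 | 97–99% |
| 0 vs 2 | 5 | 0 | 5% | 4.29 | 97–99% |
| 1 vs 3 | 5 | 3.0 | 65% | 4.29 | 97–99% |
| 1 vs 3 | 6 | 5.0 | 97.5% | 3.93 | 95–98% |
| 2 vs 4 | 4 | 3.75 | 84% | 4.29 | 97–99% |
| 2 vs 4 | 5 | 6.0 | 99.7% | 3.86 | 94–98% |
| 2 vs 4 | 6 | 5.0 | 97.5% | 3.21 | 83–92% |

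(100 per arm.) The week-7 gap runs from 0 to 6.0 points, whereas the weekly mean stays between 3.2 and 4.3.

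**A second curve shape.** Take an exponential approach to a common plateau with half-time h, scaled so that controls reach the protocol's 13 points at week 7. With starts at weeks 0 versus 2 and h from 1 to 6 weeks, the week-7 gap is 0.3 to 3.4 points and the weeks 1–7 mean gap is 3.8 to 4.5. For h = 1: plateau = 13/(1 − 2⁻⁵) = 13.4; gap = 13.4 × (2⁻⁵ − 2⁻⁷) = 0.3. With starts at weeks 2 versus 4, the week-7 gap is 1.4 to 3.6 points for h of 1 to 2 weeks, and 4.8 or more for h of 3 weeks or longer. The same dependence on trajectory appears.

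**Does the weekly average isolate speed?** No. If both arms improve linearly from the same start to 17.5 and 13 at week 7, with no head start, the mean gap is 4.5 × (1 + 2 + … + 7)/(7 × 7) = 4.5 × 28/49 = 2.6 points.

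**The case against.** The strongest reply is that a zero effect at week 7 comes from particular curves. Those scenarios let improvement begin before the median patient reaches the therapeutic range. If it begins at the protocol's medians of 2 and 4 weeks, week 7 keeps 84% to 99.7% power, and for rises of 5 or 6 weeks it has more power than the weekly average. The protocol also does not model a common plateau. Section 2.4 expects 17.5 versus 13 points, and the Summary and Section 1 say that delay ultimately lowers the chance of remission or recovery. Week 7 captures that benefit, and the 63 per group rests on it. All of this stands, and it limits the size of the loss. It does not turn a week-7 change into evidence on timing.

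A reader might infer that the trial cannot answer a question its funder required. The documents do not support that. Section 2.4 describes the funder's condition as questions about depression scores and side effects, without the timing wording, and the week-7 reduction answers the depression question as it was sized.

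A reader might also infer that the weekly average should replace week 7. It should not: the average mixes speed with extent, as the 2.6-point result shows.

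**Conclusion.** The mismatch stands. Objective and hypothesis concern earlier reduction, while the protocol fixes one week-7 change as the only depression outcome and leaves the weekly scores without a timing analysis. Because both endpoint and analysis are defined in the protocol, this is not a detail left to a statistical analysis plan.

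The cost in power cannot be given as one number. It ranges from complete loss to none, depending on when improvement starts and how fast it levels off, and the 5% figure is one corner of that range. The calculations assume that a 2-week lead in drug levels becomes a 2-week shift in symptoms, SD 9 at every visit, correlation 0.5 to 0.7, and 100 analysed per arm. The interpretive gap needs none of these assumptions. This is a secondary outcome; the primary comparison is unaffected.

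**What to change.** Keep the week-7 HAM-D reduction as the outcome on which the 63 per group rests. Add to Sections 6.1.2 and 8.2 a pre-specified timing outcome for HAM-D and, likewise, QIDS-SR: a repeated-measures model over weeks 1 to 7 that reports the arm difference at each week and the equal-weight average of those differences. State that the average is read together with week 7, because it reflects both speed and extent.

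If no timing outcome is added, reword the objective to *greater reduction of depressive symptoms at week 7* and make no claim of earlier reduction.

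The cost is one further secondary analysis and a model that the protocol does not now have for HAM-D. No new assessments are needed and the sample size is unchanged. The average is less sensitive than week 7 when improvement is slow or late.

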| Plasma for storage          |                                                                                                |               | x      |             |              |              |              |              |              | x            |
| Physical examination        | x                                                                                              |               |        |             |              |              |              |              |              |              |
|                             |                                                                                                |               |        |             |              |              |              |              |              |              |
| SRRS-6 (retardation)        |                                                                                                |               | x      |             |              |              |              |              |              | x            |
| Medication prescribed (TCA) |                                                                                                |               | x      | x           | x            | x            | x            | x            | x            | x            |
| Plasma levels               | 12 hours after first dose and repeated at steady state until primary endpoint has been reached |               |        |             |              |              |              |              |              |              |
| Adverse effects (ASEC)      |                                                                                                |               | x      | x           | x            | x            | x            | x            | x            | x            |
| HAM-D/QIDS                  | x                                                                                              |               | x      | x           | x            | x            | x            | x            | x            | x            |
| EQ5D and SF36               |                                                                                                |               | x      |             | x            |              | x            |              | x            |              |

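### The day-0 ASEC rating is collected before the first TCA dose but goes unused: the peak side-effect score is compared by an unadjusted test, and its window for ASEC is not stated

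*Protocol*

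**What the plan says.** Protocol section 6.1.2(b) sets the endpoint as the "Highest level of side effects" on ASEC and on FIBSER, both rated by the patient. It mentions neither a baseline nor a time window. Item (a) of the same list, by contrast, defines the depression outcome as baseline minus week 7.

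The schedule table in section 6.3 has a row "Adverse effects (ASEC") with eight crosses, from visit 2 (day 0) to visit 9 (day 49). FIBSER has no row of its own. The visit description in section 6.3 reads "Visit 2: Baseline (start TCA therapy). Completion of baseline assessments of secondary clinical outcome measures". It adds that "TCAs will be initially prescribed once daily in the evening", so a rating made at that visit normally precedes the first dose. It also says "The time period between visits 1 and 2 will be used for washout of psychiatric drugs", limited to drugs that failed or that interfere with study medication. Visits 3 to 9 are described separately as the treatment phase.

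Section 8.2 states: "The secondary continuous outcomes will be analysed by either student's t-test or Mann Withney U test". For FIBSER it takes the highest level within the drug-treatment period; ASEC gets no such sentence. Section 6.2 plans adjustment only for gender, age and sociocultural differences, and only if they are imbalanced.

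**The concern.** A symptom checklist filled in before any TCA has been taken cannot record TCA side effects. In severe depression, sometimes just after washout of another drug, it can still show a score above zero. Patients who score high for these reasons on day 0 are likely to score high in weeks 1 to 7 as well. A peak score with no reference to day 0 therefore mixes drug effects with each patient's own symptom level, and an unadjusted test treats that level as noise.

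The ASEC window is a second, smaller gap. An analyst who took the maximum over all scheduled ratings would include day 0, where the dosing strategy can have had no effect.

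Lower rates of adverse effects are the first-listed secondary objective, and section 2.4 says the funder required a sample large enough to answer the side-effect question. It is worth not losing precision on it when the data to avoid this are already scheduled.

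**Working it through.** **1. The plan's own figure.** Inputs from section 2.4: FIBSER 2.98 versus 2.04, SD 1.88, with 5% two-sided alpha and 80% power (stated there for the primary outcome and assumed to carry over).

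- Standardised difference: (2.98 − 2.04) / 1.88 = 0.94 / 1.88 = 0.50.
- n per group = 2 × (1.960 + 0.842)² / 0.50² = 2 × 7.85 / 0.25 = 62.8, rounded up to 63.

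The stated 63 per group reproduces. It rests on FIBSER, so nothing below changes it.

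**2. Gain from using day-0 ASEC as a covariate.** The documents give no ASEC mean, SD or correlation, so the correlation ρ between the day-0 score and the post-dose peak is an assumption. Adjustment multiplies the residual variance by (1 − ρ²), so the standardised effect grows by 1/√(1 − ρ²), equivalent to multiplying the sample size by 1/(1 − ρ²).

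| ρ | Standardised effect | Equivalent sample size |
|---|---|---|
| 0.40 | 1/√0.84 = 1.09 | 1/0.84 = 1.19 |
| 0.60 | 1/√0.64 = 1.25 | 1/0.64 = 1.56 |

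The range 0.40 to 0.60 comes from simulating one pre-dose and seven weekly post-dose ratings with a within-patient correlation of 0.3 and 0.5 between any two ratings. With the planned 100 per arm, the adjusted ASEC comparison would be as precise as an unadjusted one with about 119 to 156 per arm. The gain is the same whether or not anyone would have counted day 0.

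**3. Cost of counting day 0 in the peak.** Same model (visit-level SD 1, true arm difference 0.5 SD at every post-dose visit). Each entry is the loss in the mean arm difference when the maximum runs over eight ratings instead of seven. Levels are relative to an untreated level of 0.

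| Day 0 | Control on TCA | Intervention on TCA | Loss |
|---|---|---|---|
| 0 | +1.0 | +0.5 | about 2–3% |
| 0 | +0.5 | 0 | about 8% |
| +0.5 | +1.0 | +0.5 | about 8% |
| 0 | 0 | −0.5 | about 19–20% |
| +1.0 | 0 | −0.5 | about 54–64% |

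In the first three rows control patients score higher on TCA than on day 0, and the loss is small. In the last two, on-treatment symptoms in both arms are at or below their day-0 level; only there does the loss reach about 20% or more.

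**The case against.** **The protocol never says that day 0 counts.** A reader might infer that the day-0 rating is part of the peak and that the ASEC comparison thereby loses half its effect or more. The documents do not support this. Section 6.3 calls visit 2 the baseline and separates it from the treatment phase, and section 8.2 ties the FIBSER peak to the drug-treatment period. A sensible analyst would probably read ASEC the same way. What stands is that the ASEC window is not written down. The large loss also needs symptoms on a TCA to be no higher than before it, which sits badly with the adverse effects described in section 1.

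**The unadjusted test is valid.** This is correct. Randomisation balances pre-treatment symptoms in expectation, so a reader who inferred bias towards one arm would be wrong.

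**ASEC is not the scale the trial was sized on.** Also correct. The sample-size argument uses FIBSER, and FIBSER is the only side-effect scale that section 8.2 names. The importance of the side-effect question does not carry over in full to ASEC.

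**Covariates are often left to an analysis plan.** They are, but here the protocol itself names an unadjusted test and a short list of conditional adjustments without baseline ASEC. An analysis plan would have to depart from that wording.

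**Washout affects only some patients**, and how much it adds on day 0 is unknown. The argument for adjustment does not need it: any stable difference between patients in symptom level is enough.

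**Conclusion.** The point holds as a matter of efficiency and of one undefined window. The protocol schedules a pre-dose ASEC rating and gives it no role in an unadjusted comparison of peak scores. Using it would raise the standardised ASEC effect by about 9 to 25%, provided its correlation with the later peak lies between 0.40 and 0.60. That range is assumed, and a weaker correlation would bring less. Counting day 0 in the peak, which the text leaves open for ASEC but does not prescribe, would cost about 2 to 8% in the scenarios where TCA raises symptoms above their day-0 level.

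Excluding day 0 alone would not be enough, because pre-existing symptoms that persist still enter the ratings of weeks 1 to 7. The planned test is valid, and the primary outcome is not touched.

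**What to change.** - **Section 6.1.2(b):** define the ASEC endpoint as the highest score over visits 3 to 9 (days 7 to 49), with day 0 excluded.
- **Section 8.2:** compare arms on that score with the day-0 ASEC score as covariate (ANCOVA), or by a rank-based ANCOVA if the distribution is clearly non-normal. This keeps the protocol's existing provision for non-normal data.

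The cost is two sentences of wording, with no new ratings. The small downside is a model in place of a two-sample test. The change should be made before outcome data are compared by arm.
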